### Quality control

2.15

An independent quality control team will be set up for training 4 clinical research coordinators who are responsible for enrolling patients, acquiring informed consent, and requesting randomization. The training contents include patient recruitment, disease assessment, and data collection, which will minimize selection bias. In the process of data collection, patients’ combined medication and nonintervention treatment will be strictly noted, and the influence of the above-mentioned interfering factors will be excluded in the statistical analysis. The quality control team will also be answerable for the long-term communication and health education of patients. The above measures will help to improve compliance of patients and reduce the lost rate of follow-up.

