### Study design

2.1

This is a multicenter, randomized, placebo-controlled, double blind trial. A total of 190 patients meeting the inclusive criteria will be recruited and then randomly allocated into 2 groups in a 1:1 ratio using SPSS 25.0 (IBM, USA) for Windows (Chicago, IL, USA). Both groups will receive standard modern rehabilitation treatment according to the “Chinese Guidelines for Stroke Rehabilitation” (2011 version).^[21]^ Patients will stick to the treatment they previously have had, and will be given present general treatment when acute exacerbation of stroke occurs during the trial. The intervention group will receive PLD fumigation treatment, while the control group will receive placebo fumigation treatment. The treatments will be taken once a day lasting 30 minutes, 5 days per week. An objective biomechanical parameter, the medial plantar area (metatarsal 1+ metatarsal 2 + heel medial) from the RSSCAN gait system, will be used as the primary measure to assess the outcome. Scores of Berg Balance Scale (BBS), Fugl-Meyer assessment, Modified Ashworth Scale, Barthel Index, and Stroke-Specific Quality of Life Scale (SSQOL) will be used as the secondary measure to assess the outcome. All assessments will be conducted at baseline, a 4-week treatment and a 3-month follow-up. All participants will provide signed informed consent before proceeding with the trial. The flow chart of this trial is summarized in Fig. 1. The study timeline and event schedule are set up according to the Standard Protocol Items: Recommendations for Interventional Trials (SPIRIT) 2013 Statement (Additional file 1), as detailed in Table 1.^[22]^

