All patients in 2 groups will receive the same standardized modern rehabilitation treatment according to the “Chinese Guidelines for Stroke Rehabilitation” (2011 version). The main content of modern rehabilitation techniques is Bobath method and proprioceptive neurodevelopmental facilitation technique, which includes good limb position, muscle strength and joint activity training, knee-ankle joint control training, weight loss gait training, and so on. Five qualified and experienced rehabilitation specialists in 3 trial sites will select and conduct appropriate treatment programs according to the participants’ symptoms. All of them will receive the unified training before the start of the trial. Meanwhile, the patients will stick to the treatment they previously had, and will be given present general treatment if acute exacerbation of stroke occurs during the trial.

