### Follow-up

2.10

After finishing the 4-week treatment, all patients will enter the 3-month follow-up period. In view of the particularity of stroke rehabilitation and the ethical factors that need to be considered, patients can receive other possible salutary rehabilitation treatment except for the prohibition of additional fumigation treatment. During the 3-month follow-up period, patients will be required to fill out a form to record their specific recovery process during this period. At the end of the follow-up, all forms will be returned to the researchers for evaluation.

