### Statistical analysis

2.14

Statisticians who are independent from the trial will be responsible for the statistical analysis. The SPSS 25.0 (IBM, USA) for Windows (Chicago, IL, USA) will be used. Categorical variables will be presented with frequencies or percentages and continuous variables will be presented as the mean and standard deviation. The analysis will mainly compare efficacy between the intervention group and the control group, including primary and secondary outcomes. Changes in all outcome measurements of before and after the treatment and of the between group will be analyzed. The demographic and clinical characteristics of the 2 groups will be compared at baseline applying unpaired 2 sample *t*-tests (continuous data) and Chi-square analysis (categorical data). Rank sum test will be used when the normal distribution hypothesis is not met. Considering some participants may fail follow-up, we will conduct both intention-to-treat analysis and per-protocol analysis. The intention-to-treat analysis will include all the participants. The missing data will be treated by multiple imputations. The per-protocol analysis will incorporate the participants who follow all the time points outcome measurement and fully comply with the treatment schedule in the intervention group. The statistical significance threshold will be set at 0.05 (2-sided), with 95% confidence intervals.

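### The commitment to exclude the influence of other treatment covers treatment started after randomisation, and for that part the analysis would no longer estimate the intention-to-treat effect, chiefly at the 3-month follow-up

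*Protocol article*

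**What the plan says.** Four parts of the protocol article bear on this.

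- **Quality control (2.15).** "In the process of data collection, patients’ combined medication and nonintervention treatment will be strictly noted", and then "the influence of the above-mentioned interfering factors will be excluded in the statistical analysis". The sentence does not say whether this means dropping patients, dropping data or adjusting for use. It names no outcome, visit or analysis set, and it is not confined to a supplementary analysis.
- **Follow-up (2.10).** Once the 4 weeks of treatment are over, "patients can receive other possible salutary rehabilitation treatment except for the prohibition of additional fumigation treatment".
- **Interventions (2.9), and Study design (2.1) in similar terms.** "the patients will stick to the treatment they previously had, and will be given present general treatment if acute exacerbation of stroke occurs". This covers both treatment carried over from before randomisation and treatment that begins during the trial.
- **Statistical analysis (2.14).** "The intention-to-treat analysis will include all the participants"; "The missing data will be treated by multiple imputations". The per-protocol set is defined differently: "The per-protocol analysis will incorporate the participants who follow all the time points outcome measurement and fully comply with the treatment schedule". Neither set refers to concomitant treatment.

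On timing, Study design states: "All assessments will be conducted at baseline, a 4-week treatment and a 3-month follow-up". Table 1 schedules the primary outcome, medial plantar area, at all three visits.

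**The concern.** An ITT comparison estimates the effect of being assigned to one arm or the other, whatever else patients go on to receive. Treatment begun after randomisation is part of what follows from assignment. A patient who recovers poorly may seek more rehabilitation. If the study treatment works, fewer patients in the intervention arm will recover poorly, so uptake will differ by arm because of the treatment itself.

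Removing the influence of that uptake, by either obvious method, conditions on something that assignment may have changed. The groups compared are then no longer those formed by randomisation. The estimate may be attenuated, or it may be biased in another direction if uptake differs by arm for other reasons. Dropping users also costs power. And because no method is fixed, the choice of whom to drop or what to adjust for could be made after the data are seen.

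**Working it through.** **1. The plan's own figure.** Inputs from Sample size (2.6): difference 1.21, SDs 2.12 and 2.46, α = 0.05, power 90%. Statistical analysis (2.14) gives the test as two-sided.

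- Pooled variance = (2.12² + 2.46²)/2 = 5.273, so SD = 2.296 and the standardised effect is 1.21/2.296 = 0.527.
- n = 2 × (1.960 + 1.282)² × 5.273 / 1.21² = 75.7, i.e. 76 per group.
- 76/0.80 = 95 per group, 190 in total. The stated figures reproduce; power at 76 per group is 90.1%.

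**2. Which treatment starts when.**

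| Treatment | Starts | Can be removed without leaving ITT? |
|---|---|---|
| Earlier treatment that continues (2.1, 2.9) | Before randomisation | Yes, as a baseline covariate |
| Treatment of an acute exacerbation (2.1, 2.9) | After randomisation | No |
| Other rehabilitation in follow-up (2.10) | After the 4-week treatment | No |

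The permission in 2.10 cannot affect the 4-week measurement, so the problem lies chiefly at the 3-month follow-up.

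**3. Two readings against 2.14.** Dropping users removes randomised patients and directly contradicts the statement on who is included. Adjusting for use retains everyone, so that statement is met, but the coefficient for arm is then a comparison at equal uptake and not the effect of assignment. The per-protocol definition does not accommodate either reading.

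**4. Size of bias: illustrations only.** The article gives no uptake rates or correlations, so these are assumed.

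*Moderate case (simulation).* True difference 1.21; correlation between 4-week and follow-up values 0.5–0.7; base uptake 20–40%; a worse 4-week value raises uptake by 0.5–1.0 in log-odds per SD; the other treatment itself does not change the outcome. Dropping users gives 1.07–1.19 and adjusting for use gives the same range. Attenuation is 1 − 1.19/1.21 ≈ 2% to 1 − 1.07/1.21 ≈ 12%. In one of these settings uptake is 32% in the intervention arm and 42% in the control arm.

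*No-effect case.* With a true difference of 0 and uptake unrelated to arm, both methods give a difference of 0 within simulation error (at most 0.01 in size).

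*Extreme case.* Uptake is fixed exactly by the final outcome: the worst 30% of controls, and everyone below the same threshold in the intervention arm, are dropped.
- Control cut at −0.524 SD: mean of those kept = 0.497.
- Intervention cut at −0.524 − 0.527 = −1.051 SD (14.7% dropped): mean of those kept, relative to the arm mean = 0.269.
- Effect = 0.527 + 0.269 − 0.497 = 0.299 SD, a fall of 43%.

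*Same cut, correlation 0.5 between uptake tendency and outcome.* If treatment shifts uptake only through that correlation, the arm shift is 0.5 × 0.527 = 0.263 SD and the intervention cut is −0.788 (21.5% dropped; mean of those kept 0.373). Effect = 0.527 − 0.5 × (0.497 − 0.373) = 0.465 SD, a fall of 12%. If instead the full 0.527 SD shift acts on uptake, the effect is 0.527 − 0.5 × (0.497 − 0.269) = 0.413 SD, a fall of 22%.

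**5. Power if users are dropped.** This is a separate scenario with equal loss in both arms and an assumed share. Starting from 76 per group, with the normal approximation:

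| Dropped | Left per group | Power |
|---|---|---|
| 10% | 68.4 | 86.9% |
| 20% | 60.8 | 82.8% |
| 30% | 53.2 | 77.6% |
| 40% | 45.6 | 71.1% |

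A t-test with 53 per group gives 76.7%, so about 77% for the 30% row.

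**The case against.** The sentence is brief and sits among statements on staff training. The Statistical analysis section contains no such exclusion, and a condensed article may leave the method to a fuller document. A reader might infer from the sentence that patients will be dropped and the randomised comparison broken. The article does not say that.

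Three further points stand:

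- Concomitant medication includes treatment in use before randomisation, and adjusting for that is legitimate.
- The permission for other rehabilitation begins only after the 4-week treatment. Before then both arms receive the same standardised rehabilitation, so 2.10 is no evidence of a problem at 4 weeks.
- Covariate adjustment does not contradict the statement that all participants are included. Only dropping patients would.

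What does not stand is that the missing detail disposes of the matter. The difficulty is a stated rule, not an absent one. An analysis plan that follows the rule for treatment begun after randomisation gives up the ITT effect, and one that ignores it departs from the published protocol.

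**Conclusion.** The point holds for treatment started after randomisation, and chiefly for the 3-month follow-up. As written, the commitment in 2.15 cannot be carried out on that treatment while also estimating the ITT effect that 2.14 promises. It does not touch adjustment for treatment in use at baseline.

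The size and direction of bias cannot be settled from the article. Under the assumptions shown, attenuation is nil with no treatment effect and uptake unrelated to arm, about 2–12% in the moderate simulations, and about 43% when uptake follows the outcome exactly. A reader might take the last figure as the expected bias. It is a limiting case, and the same cut-off with a correlation of 0.5 gives about 12% or 22%, depending on how treatment acts on uptake. The fall in power from 90% to about 77% applies only if 30% of each arm were dropped, which the article does not state.

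**What to change.** Replace the sentence in Quality control (2.15) with wording such as:

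> Concomitant medication and non-study rehabilitation will be recorded and tabulated by arm. The primary ITT analysis will neither exclude participants for, nor adjust for, treatment started after randomisation; any analysis that removes the influence of such treatment is supplementary, with its assumptions stated.

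The same statement should be carried into Statistical analysis (2.14) so that the two sections agree. Adjustment for treatment in use at baseline remains open. The cost is a change of wording: the data are already to be collected, no rule on permitted treatment changes, and the sample size of 190 is unaffected.

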## Discussion

3

Although PSS seriously affects the life quality of stroke patients during the recovery periods, effective treatment is still lacking in clinics. At present, numerous domestic and foreign scholars think that exercise therapy is the basic treatment for PSS, however, the actual effect is less than expected. Oral or intrathecal injection of baclofen is also a common clinical method.^[24,25]^ Its effect is relatively significant, but it will also have an impact on normal muscle strength, which is not conducive to rehabilitation training. Therefore, seeking an effective treatment with few side effects appears to be particularly important. In China, traditional Chinese medicine fumigation therapy is widely used in clinics because of its characteristics of external treatment and direct action to the disease location. Previous study had shown that the application of traditional Chinese medicine fumigation therapy in the rehabilitation of PSS had a good theoretical basis and certain therapeutic advantages.^[26]^ However, there are few current studies on the application of PLD fumigation treatment of PSS, and the curative effect needs to be supported by the evidence of clinical trials. This study was designed to determine its real efficacy.

To achieve the best performance in the field, the RSSCAN gait system used to be designed for providing accurate and objective biomechanical parameters to formulate and improve athletes’ gait.^[27]^ Surprisingly, researches revealed that the application of RSSCAN gait system in clinical studies of diabetes, multiple sclerosis, and knee osteoarthritis also achieved satisfactory results by providing quantitative assessments.^[28]^ Based on it, we hope to determine the real effect of PLD fumigation treatment of PSS through the objective biomechanical parameters of the system. At the same time, the changes of parameters before and after treatment may also explain the biomechanical mechanisms under its curative effect.

Some limitations are inevitable in this study. Firstly, despite assessor-blinding, several patients who had been fumigated with traditional Chinese medicine will likely know which group they belong to according to the smell of the steam. Thus, we will select patients who have never received traditional Chinese medicine fumigation treatment before and keep patients separate from each other. Secondly, as this study is intended as a pilot study for further larger clinical studies, sample size is another limitation.

The results of this study are expected to verify the clinical effect of PLD fumigation treatment for strephenopodia after stroke, and to explore the related biomechanical mechanisms by objective evaluation parameter. The detailed interpretations of data in the trial will provide foundations for future larger clinical studies.
